### Intervention

2.5

After signing the inform consent, participants in both groups will receive a pretest to obtain information on the frequency of analgesic used, the VAS during rest and activity, Western Ontario McMaster Universities Osteoarthritis Index (WOMAC), Knee injury and Osteoarthritis Outcome Score (KOOS), body composition analysis, knee range of motion test, quadriceps muscle stiffness, one-leg standing with eyes open test, and the 30-s chair stand test.

The study participants will receive 12 sessions of LA and EA (the treatment group) or sham LA and EA (the control group) over 4 weeks. LA will be performed using a gallium aluminum arsenide LaserPen (maximal power, 150 mW; wavelength, 810 nm; area of probe, 0.03 cm^2^; power density, 5 W/cm^2^; and pulsed-wave; RJ-Laser, Reimers & Janssen GmbH, Waldkirch, Germany). The LA treatment will be applied to EX-LE5, ST35, and BL40 (Fig. 2) for 80 s, at 150 mW, to deliver a total treatment dose of 6 J/cm^2^ (Fig. 3). An experienced physician who has adequate training and a license in practicing Chinese medicine in Taiwan for more than 7 years will perform all LA treatments. Both the physician and patients will wear necessary protective gear. The control group will undergo the same procedure as the treatment group but with an inactive LaserPen (with the indicative light on but no laser output). Both of the LaserPen in two groups are labeled with A and B, and the physical appearance of both LaserPens will be the same to eliminate any bias from physicians and the participants.

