
The reason for patients who are not completing the follow-up visit or dropping out of this study, such as adverse events, suboptimal response to therapy, failure to return for following up, and refusal to receive treatment will be recorded. The potential adverse events will also be recorded although only 6 J/acupoint will be delivered to each acupoint.

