Among many of the mechanisms of KOA, synovial inflammation (synovitis), abnormal bone structure, osteophytes, and bone marrow lesions can result in knee pain.^[5]^ It is possible that EA treatments could lead to activation of the nervous system and inhibition of inflammatory and neuropathic pain by desensitizing peripheral nociceptors and reducing pro-inflammatory cytokines.^[51]^ The clinical effects of LA are likely to encompass anti-inflammatory, neural modulation, cell healing and regeneration effects.^[23]^ Both LA and EA have anti-inflammatory and neural modulation, which may decrease knee pain in KOA. Conversely, exercise therapy can reduce knee pain in patients with KOA and these exercise therapies are focused on improving aerobic capacity and quadriceps muscle strength.^[17]^ LA has an analgesic effect and can improve the function and muscle strength of quadriceps in KOA.^[37]^ Besides, LA and EA have many advantages, including low risks of complications, pain, cost, and high analgesic efficacy. Although some studies confirmed such beneficial effects of LA or EA in improving KOA symptoms, the combined effect of EA and LA on KOA remains elusive.

In this study protocol, we will use LA at 6 J/acupoint delivered with an 810 nm laser in addition to EA treatment for 4 weeks. LA treatments are poised to heal damaged chondrocytes, which are more susceptible to pain stimulation.^[59]^ The outcome evaluations will include analyses of subjective symptoms, quadriceps muscle functions, and body composition measurements. In conclusion, we hypothesize that a combination of LA and EA is expected to be more effective than these therapies alone in alleviating knee pain and stiffness and increasing muscle strength of lower limbs, which can further improve the balance and quality of life. Moreover, this combined therapy may also benefit in reducing the need for total knee replacement therapy and further decrease the cost coverage of national health insurance.

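### The laser dose is given as 6 J/cm² in one place and 6 J per acupoint in two others; on the stated probe area these differ 33-fold, and the 6 J/cm² does not follow from its own settings

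*Protocol article*

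**What the plan says.** Section 2.5 (Intervention) describes the laser pen with "maximal power, 150 mW; wavelength, 810 nm" and "area of probe, 0.03 cm^2^; power density, 5 W/cm^2^; and pulsed-wave". It names three laser points: "The LA treatment will be applied to EX-LE5, ST35, and BL40". It then gives the exposure and the resulting dose: "for 80 s, at 150 mW, to deliver a total treatment dose of 6 J/cm^2".

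Two later places give the dose in another unit. The adverse-event text at the end of section 2.6 (Outcome measurements) says "only 6 J/acupoint will be delivered to each acupoint". The Discussion says "we will use LA at 6 J/acupoint delivered with an 810 nm laser".

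The article gives no duty cycle for the pulsed output. Apart from calling 150 mW the maximal power, it does not say whether that figure is peak or average. It does not state outright whether the 80 s is for each point or for all three together.

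**The concern.** Joules per acupoint measure energy; joules per square centimetre measure energy per unit area. The same number, 6, appears with both units, as though they were interchangeable. They would be numerically equal only over an area of 1 cm², and the article gives 0.03 cm².

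The laser dose is the experimental variable. Both arms receive the same electroacupuncture and the same laser procedure, and the arms are meant to differ only in whether the pen emits. The Discussion says that missing information, energy density included, made one meta-analysis of laser acupuncture hard to interpret. It separately suggests that differing laser dosage may be among the reasons for ambiguous results across studies. It also cites benefit in a later meta-analysis at 4 to 8 J. A reader who wants to place this trial against that range, replicate the treatment or pool the result by dose needs one usable figure, and the article offers two that conflict.

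**Working it through.** **Inputs, all from section 2.5 unless noted**
- Power P = 0.150 W (called maximal)
- Probe area A = 0.03 cm²
- Power density = 5 W/cm²
- Exposure t = 80 s
- Stated dose: 6 J/cm² (section 2.5); 6 J per acupoint (section 2.6 and Discussion)
- Duty cycle d: not stated, so varied below as an assumption

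**Formulas.** Power density = P/A. Energy E = P × t × d. Fluence = E/A.

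**Step 1: the figure that reproduces.** 0.150/0.03 = 5 W/cm², as stated. The power, the probe area and the power density agree with one another.

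**Step 2: the two stated doses compared.** This step uses only the area.
- 6 J per acupoint: 6/0.03 = 200 J/cm²
- 6 J/cm²: 6 × 0.03 = 0.18 J
- Ratio: 200/6 = 6/0.18 = 33.3

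Power, time and duty cycle do not enter, so no assumption about pulsing alters the ratio.

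**Step 3: the stated 6 J/cm² tested against its own settings.** With 80 s at each point:

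| Assumed duty cycle | J per point | J/cm² | Multiple of 6 J/cm² |
|---|---|---|---|
| 100% (150 mW is the average) | 12 | 400 | 66.7 |
| 75% | 9 | 300 | 50 |
| 50% | 6 | 200 | 33.3 |
| 25% | 3 | 100 | 16.7 |
| 1.5% | 0.18 | 6 | 1 |

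The first row can be checked another way: 5 W/cm² × 80 s = 400 J/cm². To obtain 6 J/cm² from these settings, the duty cycle would have to be 0.18/12 = 1.5%, or the exposure at 5 W/cm² only 6/5 = 1.2 s instead of 80 s.

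**Step 4: sharing the 80 s.** If the 80 s were divided over the three points, which the article does not say, continuous output would give 12/3 = 4 J and 4/0.03 = 133 J/cm² per point. That matches neither stated dose.

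**The case against.** The strongest defence is that the device is pulsed and 150 mW is its maximal power. Under an assumed 50% duty cycle the settings give exactly 6 J per point, in agreement with section 2.6 and the Discussion. The only fault would then be a wrong unit in section 2.5. This stands as far as it goes: the settings cannot be said to contradict 6 J per acupoint. It does not rescue 6 J/cm², which at that duty cycle is still 33-fold below the implied fluence.

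One could also suppose that J/cm² refers to a treated area of 1 cm² and not to the probe. Then 6 J and 6 J/cm² would coincide. But 150 mW over 1 cm² is 0.15 W/cm², not the stated 5 W/cm², and no such area appears in the article.

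Some stronger conclusions are tempting, and the article does not support them:
- **That the settings deliver 12 J, or 67 times the stated fluence.** This needs 150 mW to be the average power and 80 s to be the time at each point. Neither is stated, so these figures are upper bounds and not a proven third dose.
- **That all the doses are 33 to 67 times apart.** Those multiples hold only against 6 J/cm². Between 6 J and 12 J the factor is 2.
- **That each point gets 4 J.** Nothing in the text says the 80 s is shared.
- **That the intervention is undefined.** Device, wavelength, maximal power, probe area, time, acupoints and number of sessions are all given. The fault lies in the stated dose and its unit.
- **That safety recording depends on the figure.** Section 2.6 records adverse events regardless, and section 2.5 has them recorded after every session.

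The absence of a duty cycle is not itself a fault, since a condensed article may leave it to the full protocol. Nor does the inconsistency touch randomisation, blinding or the sample size.

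**Conclusion.** The laser dose is stated inconsistently. The 33-fold conflict between 6 J/cm² and 6 J per acupoint rests only on the stated probe area, which the stated power and power density confirm. In addition, 6 J/cm² cannot be obtained from 150 mW for 80 s without a duty cycle of about 1.5%. Assumed duty cycles from 25% to 100%, with 80 s at each point, give 100 to 400 J/cm².

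The consequence is for interpretation. Against the 4 to 8 J cited in the Discussion, 6 J lies inside the range and 0.18 J far below it; 12 J, if it applied, would lie above. Because this is a wrong figure in the methods for the one component that separates the arms, it should be corrected. No view is taken on which dose is right.

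**What to change.** Check the device setting actually used, then reconcile the dose statements in section 2.5, section 2.6 and the Discussion with it. Give one mutually consistent set of values: average power (making clear how the pulsing enters), exposure time per acupoint, joules per acupoint and J/cm², with the area to which the last refers. Use the same set throughout, including in the adverse-event sentence of section 2.6.

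The cost is one check of the device and corrections to three sentences. The design, the sample size and the analysis are unaffected.

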**Figure 2 F2:**
[figure not shown]
Acupoints used for knee osteoarthritis in this study. The blue color acupoints correspond to interventions with laser acupuncture, whereas the red color acupoints correspond to intervention with acupuncture.

**Figure 3 F3:**
[figure not shown]
Laser acupuncture performed at EX-LE5 acupoint by the LaserPen device.

EA is a combination of acupuncture and transcutaneous electrical nerve stimulator. The transcutaneous electrical nerve stimulator device is produced by the Ching Ming Medical Device Company. This machine (ID number 001147) is verified by the Ministry of Health and Welfare in Taiwan. The acupuncture will be first performed on GB33, GB34, SP9, SP10, and ST36 sites (Fig. 2). Subsequently, transcutaneous electrical nerve stimulator will be used on the GB33, GB34, SP9, and SP10 sites. There are electrical outputs in a transcutaneous electrical nerve stimulator, and each electric output has two lines (black and red) representing the positive and negative pole, respectively (Fig. 4). When both electrical outputs are connected to paired needles, it produces electric currents to stimulate the specific acupoints. The electric wave mode will be continuous wave to achieve stable stimulation, at a frequency of 2 Hz for 15 min. The power of the electric current will be adjusted to make each patient feel the electric stimulation but still comfortable during the treatment process. All the acupoints are selected and localized according to the guideline of WHO Standardized Acupuncture Point Location.^[33]^

**Figure 4 F4:**
[figure not shown]
Electroacupuncture performed at GB33, GB34, SP9, and SP10 acupoints by transcutaneous electrical nerve stimulator.

After treatments in each session, a designated physician will record the frequency of analgesic used, the VAS during rest and activity, the response to our therapy, and any adverse events. The patients can receive analgesics during the treatment period; however, they will be prohibited from receiving other acupuncture, rehabilitation program or knee surgery in any other clinic. If the patients do not follow these provisions, we will exclude these patients from our study protocol. On successful completion of 12 sessions, all participants will be subjected to the same exam and questionnaire as during the pretest.

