### Sample size and randomization

2.4

The necessary sample size was calculated from the result of a previous study on the effect of LLLT. In this study conducted by Al Rashoud et al, the mean difference (standard deviation) of the VAS at the baseline before the treatment were 6.4 (1.9) at the treatment group, and 5.9 (1.8) at the control group, and the mean difference (standard deviation) of the VAS after completing the treatment were 3.2 (1.7) at the treatment group, and 3.8 (2.3) at the control group.^[32]^ We aimed to achieve an effect size of 0.569, a significance level (α) of 0.05, the desired power (1 − β) of 0.80, and correlation among repetition measures of 0.5, and as such, the estimated sample size for this study was 22. Anticipating a 20% dropout rate, a total of 50 participants were recruited.

We used a randomized block design to distribute participants equally into two groups, A and B, with the help of a research randomizer (https://www.randomizer.org). Designated physicians enrolled participants who met the inclusion criteria and grouped the participants according to the result of randomizer by the website. The trial participants, outcome assessors, and data analyst will be blinded after assignment to interventions using labels A and B for the 2 groups.

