### Outcome measurements

2.6

We will evaluate the KOA patients with subjective tests and objective questionnaires at the beginning of the treatment and after 12 weeks of therapy. The data will be collected and entered into the patient's medical record in a computer, and all patient-related documents will be securely stored. Only the study-related investigators, including the physicians and the assistants will be allowed to access to the trial dataset. The primary outcomes will be the difference in the frequency of analgesic used and VAS scores during rest and activity between the treatment group and the control group. The secondary outcomes will be the difference between the control and treatment groups in terms of WOMAC, KOOS, body composition analysis, knee range of motion test, quadriceps muscle stiffness, one-leg standing with eyes open test, and the 30-s chair stand test after completing the 12 sessions of treatments.

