### Statistical analysis

2.7

All data will be presented in the form of mean ± standard deviation. The independent *t* test and chi-square tests will be used to assess and compare the baseline patient characteristics between the treatment and the control groups. Repeated measure analysis of variance and the generalized estimating equation will be used to evaluate changes in the VAS, WOMAC, KOOS, body composition, knee range of motion, rectus femoris stiffness, standing on one foot, and 30-s chair stand test between the treatment and the control groups. Statistical significance will be considered at a *P*-value of <.05. All statistical analyses will be performed with the SPSS for Windows, version 26 (Statistics 26, SPSS, IBM Corp., Chicago, IL).

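### VAS is recorded at all 12 sessions, but the plan does not say which readings or which contrast decide; one baseline-adjusted week-4 contrast would use the data better than a pre/post or all-session ANOVA

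*Protocol article*

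**What the plan says.** - **Readings taken (section 2.5).** "After treatments in each session, a designated physician will record the frequency of analgesic used, the VAS during rest and activity". The pretest battery, which includes VAS, is repeated once after the 12 sessions. Section 2.2 sets 12 sessions over 4 weeks and the abstract says three per week, so sessions 10, 11 and 12 fall in week 4.
- **Outcome (section 2.6).** VAS at rest and during activity is a primary outcome, together with analgesic frequency. No time point or summary is attached to VAS; completion of the 12 sessions is attached to the secondary outcomes. Patients are to be evaluated "at the beginning of the treatment and after 12 weeks of therapy", which conflicts with the 4 weeks in section 2.2.
- **Analysis (section 2.7).** "Repeated measure analysis of variance and the generalized estimating equation will be used to evaluate changes in the VAS" and the secondary measures. The time points and the deciding contrast are not named.
- **Sample size (section 2.4).** It uses one pre and one post VAS value from an earlier low-level laser trial, with "correlation among repetition measures of 0.5, and as such, the estimated sample size for this study was 22".

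**The concern.** The trial is small (25 per arm expected) and its pain endpoint is a self-report. Up to 14 VAS readings per patient and scale will exist: the pretest, 12 sessions and the post-test. Because section 2.7 does not say how they are used, the trial could be analysed with the pretest and post-test only, or with every session in a group-by-time test. The first ignores the session readings. The second spreads one question over 12 or 13 degrees of freedom. Both can have low power for the difference at the end of treatment. Leaving the choice open also allows the deciding time point to be picked after the data are seen.

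**Working it through.** **Inputs from the protocol (section 2.4)**
- Effect size: "We aimed to achieve an effect size of 0.569". Its type is not stated. It is read here as a standardised mean difference (d), because the source data give a difference in change of (6.4 - 3.2) - (5.9 - 3.8) = 1.1 and an SD of about 1.94, so 1.1/1.94 = 0.57.
- "a significance level (α) of 0.05", taken as two-sided, and "the desired power (1 − β) of 0.80".
- Correlation among repeated measures: 0.5, the only correlation given.
- 50 recruited with 20% dropout: 50 × 0.8 = 40 completers, or 20 per arm.

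**Assumptions:** r, the correlation among the week-4 readings, runs from 0.5 to 0.9. The effect has either plateaued by week 4 or grows linearly to session 12.

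**The plan's own figure.** The 22 reproduces as a total N from the between-groups test of a two-measurement repeated-measures ANOVA with 0.569 entered as Cohen's f. λ = 0.569² × 22 × 2/(1 + 0.5) = 9.50, giving 83.4% power; N = 20 gives 79.4%. So the sample size was built on two measurements. With 0.569 read as d, it does not reproduce as 22 per arm.

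**Repeated-measures ANOVA, group-by-time test, all correlations 0.5, 20 per arm.** λ = (20/2) × 0.569² × S/(1 - 0.5), where S is the sum of squared deviations of the effect profile (final value = 1) from its mean.

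| Readings | Profile | S | Power |
|---|---|---|---|
| Pretest and post-test | – | 0.50 | 42% |
| Pretest + 12 sessions | constant from session 1 | 0.92 | 29% |
| Pretest + 12 sessions | linear growth | 1.26 | 40% |
| Pretest + 12 sessions + post-test | constant from session 1 | 0.93 | 28% |
| Pretest + 12 sessions + post-test | linear to session 12, then held | 1.50 | 46% |

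**Baseline-adjusted contrasts, one degree of freedom, noncentral t, 20 per arm**
- Single post-test: residual variance 1 - 0.5² = 0.75 (in SD²); 0.569/√0.75 = 0.657; power 52.6%.
- Mean of sessions 10-12: residual variance (1 + 2r)/3 - 0.25. Under linear growth the effect is multiplied by (10 + 11 + 12)/36 = 0.917.

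| r | Residual variance | Standard error vs single post-test | Power, plateau (gain) | Power, linear growth (gain) |
|---|---|---|---|---|
| 0.5 | 0.417 | -25% | 77.5% (+24.9) | 70.2% (+17.6) |
| 0.7 | 0.550 | -14% | 65.7% (+13.1) | 58.2% (+5.6) |
| 0.8 | 0.617 | -9% | 60.8% (+8.2) | 53.5% (+0.9) |
| 0.9 | 0.683 | -5% | 56.4% (+3.8) | 49.4% (-3.2) |

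With 25 per arm and a plateau, 62.4% rises to 86.3%, 75.7% and 66.4% at r = 0.5, 0.7 and 0.9.

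**Sensitivity**
- Without baseline adjustment, 41.8% rises to 57.5%, 50.0% and 44.3% at r = 0.5, 0.7 and 0.9 (plateau).
- If the effect is only the post-treatment difference in the source study, 0.6/√((1.7² + 2.3²)/2) = 0.6/2.02 = 0.30, the gain is about 5-11 points at r = 0.7 down to 0.5 (adjusted, plateau).
- If every correlation, including that with baseline, is 0.7, the pre/post group-by-time test has 62% and the all-session test 48-74%. The adjusted single post-test has 69% and the adjusted week-4 mean 88% (plateau) or 82% (linear growth).

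**The case against.** - **The plan also names GEE.** A GEE can use every session reading and test a one-degree-of-freedom contrast. A reader might infer that the plan commits the comparison to one post-test reading or to an omnibus test. The documents do not support that, because section 2.7 fixes neither. The 22 itself reproduces from a one-degree-of-freedom between-groups test, not from a 12- or 13-degree-of-freedom interaction. This stands.
- **A contrast can be left to an analysis plan.** This is fair, and a fuller document may name one. The point is therefore an improvement to what section 2.7 states, not a claim that something is missing everywhere.
- **A gain of 13-25 points is not a general figure.** A reader might take it as the power given up. It holds only against a baseline-adjusted post-test that section 2.7 does not name, with a plateau and r of 0.5-0.7. The 0.5 in section 2.4 was used with two measurements and says little about sessions days apart, which may correlate more strongly. The whole range is about -3 to +25 points. This stands.
- **The gain is not free.** Session VAS is taken after treatment, so a week-4 mean may include immediate relief, while the pretest precedes any treatment. The quantity being estimated changes. This also stands and has to be accepted openly.

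None of this makes a pre/post or all-session group-by-time ANOVA a good decision rule, and nothing in section 2.7 rules either out.

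**Conclusion.** The point holds as a cheap improvement. The protocol collects 12 session readings of a primary outcome and fixes neither the readings nor the contrast that decide. At d = 0.569, correlations of 0.5 and 20 completers per arm, the ANOVA options have about 42% (pre/post) and 28-46% (all sessions) power. A baseline-adjusted single post-test has 53% and a baseline-adjusted week-4 mean 56-78% under a plateau or 49-70% under linear growth. The averaging step alone is worth about +4 to +25 points in the first case and -3 to +18 in the second. These figures rest on reading 0.569 as d, on a baseline correlation of 0.5 and on a within-week correlation that the protocol does not give. Naming one adjusted contrast is the firmer part of the advice; the extra gain from averaging is likely but not certain.

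**What to change.** 1. Reconcile the 12 weeks in section 2.6 with the 4 weeks in section 2.2, so that the end-of-treatment assessment has one stated time.
2. In sections 2.6 and 2.7, define the VAS endpoint (rest and activity each) as the patient's mean over the week-4 sessions (10, 11 and 12), with readings taken at one stated time relative to the session.
3. Compare arms by one single-degree-of-freedom contrast adjusted for pretest VAS, fitted by ANCOVA or as a GEE contrast.
4. Keep the single post-test, analysed in the same way, as a sensitivity analysis. Do not use an omnibus group-by-time test as the decision rule.

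**Cost:** no extra patient or visit; a few sentences of analysis wording and one rule on when the session reading is taken. The endpoint becomes average week-4 pain recorded after sessions, which may include immediate post-session relief. If the effect is still rising linearly, the mean lies about 8% below the final value (1 - 0.917), and the power gain vanishes at a within-week correlation slightly above 0.8.

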### Study design

2.2

This randomized controlled trial will be conducted at the Department of Chinese Medicine at the Kaohsiung Chang Gung Memorial Hospital from August 2019 to December 2020. The participants recruited from our outpatient departments will be randomly allocated to the treatment group (LA plus EA, n = 25, expected) or the control group (sham LA without laser output plus EA, n = 25, expected). All participants will receive 12 sessions of treatment over 4 weeks. The study design is depicted in Figure 1.

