### Participants

2.3

The diagnosis of KOA depends on the patient's history (age more than 50 years old, persistent knee pain, limited morning stiffness, reduce function, crepitus, restricted movement and bony enlargement)^[30]^ and radiography (osteophytes formation, joint space narrowing, subchondral bone sclerosis, and subchondral cysts).^[31]^ In this study, we recruited patients who were diagnosed with KOA, aged more than 50 years old and had knee pain for more than 3 months. Designated physicians evaluated the eligibility of all participants. Patients’ inclusion criteria for this study were based on the following factors: visual analog scale (VAS) > 3 points in daily activity, Kellgren–Lawrence Grading Scale grade is between 1 and 3 on knee X-ray, and informed consent obtained adequately. Patients’ exclusion criteria for this study were based on the following factors: history of knee arthroplasty, traumatic injury related joint deformity, body mass index more than 35, pacemaker insertion, photosensitivity, intra-articular injection or acupuncture 1 month before the enrolment, and any factors that may affect the evaluation of the outcome, such as psychiatric disorder and moderate to severe mental retardation.

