We will evaluate the frequency of analgesic used to treat knee pain after each intervention, including acetaminophen, a non-steroidal anti-inflammatory drug, or opioid drug. VAS will be used to evaluate the intensity of knee pain during activity and rest on a scale of 0 to 10, corresponding to the minimum and maximum discomfort intensity. The minimal clinical important difference (MCID) of VAS is 1.8 units,^[34]^ implying that an effective treatment will improve the VAS score by 1.8 points. WOMAC is a subscale for assessing the physical function of knee joints. There will be 17 questions with grading from 0 to 4 points for each question. Thus, the total score will be between the ranges of 0 to 68 points. Higher points correspond to more difficulties in performing a given activity. The MCID of WOMAC is 6 units.^[35]^ The KOOS is a self-administered scale and evaluates five outcomes, including pain, symptoms, activities of daily living, sport and recreation function, and knee-related quality of life. The scale is divided into five factions, including none, mild, moderate, severe, and extreme, which represent the severity of the deterioration of knee function and the impairment in daily living.^[36]^ A previous study showed that one-time LLLT had some effects on improving the knee function and muscle strength of quadriceps in KOA.^[37]^ We use Myoton-3 myometer and InBody 270 to measure muscle functions. In Myoton-3 myometer, the tip is placed on the midpoint of the patient's rectus femoris to measure muscle stiffness, representing the muscle ability to resist the changes of its shape, caused by external forces.^[38]^ InBody 270 can measure body composition, including the fraction of muscle and fat, and the muscle mass distribution of four limbs. This device will be used to evaluate the composition of thigh muscles and any possible muscle imbalance. One-leg standing with eyes open test will be used to assess balance and muscle strength of lower extremities.^[39]^ The patient will stand on one leg with their hands on hips and eyes opening for up to 120 s. We will record the time that the patient can stand on one leg under the instruction. Another functional assessment is the 30-s chair stand test, which can evaluate the muscle performance and the endurance of lower limbs.^[40]^ The patient will sit on the chair with bilateral feet stepping on the ground and hands crossed over the chest. Subsequently, the patient stands up and then sits down. Completing one standing up and then sitting down scores one, etc. We will calculate the number of times the patient can stand up and then sit down in 30 s. A designated study assistant will evaluate these tests.

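### Intra-articular injection bars entry for one month but is missing from the on-treatment prohibitions, so a knee injection during the 4-week course breaks no stated rule and is not named for recording

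*Protocol article*

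**What the plan says.** Section 2.3 (Participants) lists, among the entry exclusions, "intra-articular injection or acupuncture 1 month before the enrolment". Injection and acupuncture share one clause and one window.

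Section 2.2 (Study design) sets the course: "All participants will receive 12 sessions of treatment over 4 weeks". Section 2.5 (Intervention) places the post-test on completion of the 12 sessions.

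The rules during treatment are in section 2.5, in the text after Figure 4. First a permission: "The patients can receive analgesics during the treatment period". Then the prohibitions: "they will be prohibited from receiving other acupuncture, rehabilitation program or knee surgery in any other clinic". Then the consequence: "If the patients do not follow these provisions, we will exclude these patients from our study protocol". The same paragraph has a physician record analgesic frequency, VAS at rest and on activity, response to therapy and adverse events after each session.

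Section 2.6 (Outcome measurements) states: "The primary outcomes will be the difference in the frequency of analgesic used and VAS scores during rest and activity". It describes the analgesics counted as "including acetaminophen, a non-steroidal anti-inflammatory drug, or opioid drug".

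**The concern.** The entry rule implies that the investigators regard a knee injection within the past month as able to disturb the pain measurements. That protects the baseline. The rule for the treatment period keeps acupuncture from the same clause and adds rehabilitation and knee surgery, but drops injection. The post-treatment measurement therefore lacks the protection given to the baseline.

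An injection after randomisation could lower VAS and analgesic use for reasons unrelated to the laser. Patients need a VAS above 3 to enter, so some may look for further relief during the course. If injections follow persistent pain, they would be more frequent in the less effective arm, improve that arm's scores and shrink the observed difference. Because injection is not named for recording, a reader of the results might not be able to tell whether this had happened.

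**Working it through.** The article states no figure on this point, so there is none to reproduce. The check has three parts.

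**1. The two lists side by side**

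| Treatment | Entry exclusion, past month (2.3) | Prohibited during treatment (2.5) |
|---|---|---|
| Acupuncture | Yes | Yes (other acupuncture) |
| Intra-articular injection | Yes | Not named |
| Rehabilitation program | Not named | Yes |
| Knee surgery | Arthroplasty excluded by history, no time window | Yes |

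No other wording closes the gap:
- An injection is not naturally read as knee surgery or as a rehabilitation program.
- The general clause in 2.3 about factors that may affect outcome evaluation is an entry criterion. It does not govern conduct after enrolment.
- The analgesics in 2.6 are three drug classes, and an intra-articular agent is not named. If someone did count an injection as an analgesic, section 2.5 would expressly allow it.

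**2. The time window**

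The course lasts 4 × 7 = 28 days, and the post-test follows the twelfth session. An injection on any treatment day therefore falls within about one month of the post-test, the same interval that bars entry before baseline. Section 2.6 also speaks of assessment after 12 weeks, which conflicts with the 4-week course given elsewhere. That is a separate matter; the calculation here uses 4 weeks.

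**3. Possible size, for illustration only**

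Inputs from the article: 25 patients per arm (2.2); 20% anticipated dropout, so 25 × 0.8 = 20 per arm (2.4); minimal clinically important difference of 1.8 VAS points (2.6); post-treatment standard deviations of 1.7 and 2.3 from the study used for sample size (2.4). Assumed, because the article gives no value: an injection lowers VAS by 1 to 2 points.

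Shift in the between-group difference = assumed effect × net extra injected patients ÷ number per arm.

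Standard error of the difference in post-treatment means = √((1.7² + 2.3²)/n) = √(8.18/n), which is 0.57 for n = 25 and 0.64 for n = 20.

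| Number per arm | Assumed effect | Shift per net extra injected patient | Share of 1.8 points | Share of one standard error |
|---|---|---|---|---|
| 25 | 1 | 1/25 = 0.04 | 2.2% | 7% |
| 25 | 2 | 2/25 = 0.08 | 4.4% | 14% |
| 20 | 1 | 1/20 = 0.05 | 2.8% | 8% |
| 20 | 2 | 2/20 = 0.10 | 5.6% | 16% |

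With equal arms, the same number injected in each and the same effect, the shift is 0. No figure can be given for analgesic frequency, because the article states no expected mean or spread for it.

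**The case against.** The strongest objection is that this is an omission in a condensed article. A full protocol may carry a longer list of prohibited treatments and may well name injection. Section 2.5 lists three treatments in one sentence; it does not say that only these are barred or that everything else is allowed. This stands in part. A reader might infer that the list is closed and that the trial deliberately permits injections, but the text does not say so. What remains is that the article does not skip the topic: it states a specific rule and attaches exclusion to it. Followed as written, that rule does not reach a knee injection.

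A reader might also infer that sections 2.3 and 2.5 contradict each other. They do not. One governs eligibility and the other conduct during treatment, and both can be followed at once.

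A third tempting reading is that injections would bias the trial towards the laser. The article gives no support for this. Section 2.4 blinds participants, outcome assessors and the data analyst, and the sham device looks identical, so knowledge of allocation should not drive injection use. The remaining systematic route, more injections in the less effective arm, dilutes the contrast and costs some power. Contact at 12 sessions also makes it likely that an injection would come to light, although nothing in the article requires it to be written down.

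Finally, adding injection to the list would, on its own, bring injected patients under the exclusion rule, and exempting only them would treat them differently from patients who break the other provisions. This is correct, and the fix has to cover all of them.

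**Conclusion.** The gap is real on the text of the article and minor. Of the two treatments in the one-month entry washout, only acupuncture is carried into the on-treatment prohibitions. A knee injection during the course breaks no stated rule and is not named for recording, though it could alter VAS and analgesic use.

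The size is unknown and possibly zero. Under the assumed effect of 1 to 2 VAS points, one net extra injected patient moves the difference by at most 0.10 points, well below both the 1.8-point minimal clinically important difference and one standard error. Several net injections in one arm would be needed to matter, and the article gives no basis for expecting that. Dilution is the likely direction if injections follow persistent pain; that is also an assumption. Confidence is medium, because the full protocol might already name injection. If it does, the sponsor need only confirm it.

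**What to change.** Make three small changes.

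1. In section 2.5, add intra-articular knee injection to the prohibited treatments for the 4-week course. Analgesics stay allowed.
2. Add any knee injection to the items recorded at the existing per-session assessment, and report the number by arm.
3. State that a patient who receives an injection stays in the primary analysis as randomised, and apply the same handling to patients who break the acupuncture, rehabilitation or surgery provisions. The exclusion sentence in 2.5 then needs rewording so that it cannot remove randomised patients from the primary analysis. Without this step, adding injection to the list would create a new ground for exclusion after randomisation, possibly related to poor response.

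The cost is one added term, one recorded item and a sentence or two on analysis, with no extra visits or patients. The downside is one more restriction on patients for 4 weeks. An injection that still occurs would still dilute the contrast; recording it only makes that visible.
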